### Data collection methods

#### Baseline assessments

In addition to usual care procedures, baseline assessments take place following consent and prior to surgery.

#### Cardiovascular and significant current and past medical history

A full medical history is recorded for each patient at baseline and includes details of all clinically significant past medical conditions and all clinically significant on-going medical conditions including full cardiovascular history.

#### Physical assessment

A physical assessment of height (measured in centimetres) and weight (measured in kilograms) determines body mass index.

#### Current medications

A full list of the generic names of relevant medications taken by the patient is recorded within 14 days before surgery. The information includes frequency and dose. Changes or additions are recorded from baseline until the 12-week follow-up visit.

For patients in both trial arms, pre-operative antiplatelet drugs (including clopidogrel and aspirin) and anticoagulants (including heparin and warfarin) are discontinued 5 days prior to surgery. The exception is aspirin, which is stopped 5 days prior to surgery where possible; however, continuation until the day of surgery does not exclude a patient from the trial, and is recorded. These drugs may be re-started following surgery at the discretion of the clinical team. Dates for re-starting medications are recorded.

#### International normalized ratio (INR) checks for patients taking warfarin

Patients on warfarin have their INR checked as part of routine care on admission to hospital for their index surgery. Where an INR is ≤1.5, the patient proceeds to surgery. Where a patient’s INR is >1.5, appropriate treatment may be given and surgery may need to be delayed. The INR for patients taking warfarin must be ≤1.5 prior to surgery.

#### Demographic information

The following demographic data are recorded:AgeGenderEthnicity.

#### Blood tests

Blood tests are taken within 14 days prior to surgery and prior to randomisation:Urea and electrolytes (sodium, potassium, creatinine, urea)Pregnancy testFull blood count (haemoglobin, haematocrit, platelets, white cell count)Coagulation screen (prothrombin time (PT), prothrombin time ratio (PTR), activated partial thromboplastin time (APTT), activated partial thromboplastin time ratio (APTTR)Inflammatory markers.

Out of normal range blood parameters are assessed by the clinical team to confirm that there are no clinically significant findings that would affect continuation in the trial. The value of haemoglobin taken up to 14 days pre-surgery is used as a stratifying variable for randomisation.

Patients also have blood samples (stored as plasma) taken pre-operatively, on admission to CICU and 24 h post-operatively. These are analysed to explore the following null hypotheses:That there will be no difference between peri-operative inflammatory markers (IL-6, IL-8, IL-10) and markers of endothelial inflammation (ICAM-1 or CD62E) between those undergoing AVR via manubrium-limited ministernotomy when compared to AVR via conventional sternotomyThat there is no correlation between the number and proportion of patients who receive a RBC transfusion and the number of units transfused and peri-operative inflammatory markers (IL-6, IL-8, IL-10).

#### Echocardiogram

Results from the latest echocardiogram (echo) pre-surgery are recorded. If an echo has not been done within 39 weeks (9 months) of consent, this is repeated at baseline.

#### Pulmonary function tests

Pulmonary function tests of forced expiratory volume (FEV1) and forced vital capacity (FVC) are performed at baseline with patients sitting for both assessments. These assessments are repeated on days 3 and 4, and at 6 weeks following discharge from hospital after their index surgery.

#### EuroSCORE

Logistic EuroSCORE [24] is determined prior to randomisation to be used as a stratifying variable, with the score recorded. The elements that determined the logistic EuroSCORE pre-operatively are also recorded. EuroSCORE II [25] and the elements that determine this score are also recorded.

#### Quality of life assessment (EuroQoL EQ-5D-3L [22])

Each patient completes the EuroQoL EQ-5D-3L [21] questionnaires at baseline. If the patient is physically unable to complete the questionnaires, or the assessment is being performed over the telephone, the research team will administer them to the patient, who dictates their answers. The details of who is recording the patient’s responses are noted. Questionnaires are repeated at day 2, 6 weeks and 12 weeks (3 months) following discharge from hospital.

#### Assessment of pain

Pain is assessed within 14 days prior to index surgery using an 11-point numerical rating scale. Pain is also assessed post-operatively (daily from post-operative day 2 until the patient is deemed ‘fit for discharge’), and at follow-up (6 and 12 weeks following discharge).

### Retention of participants

Patients who withdraw have all data collected up until the point of withdrawal included in the study except where withdrawal is due to a related adverse event (AE), in which case the patient is followed until a stable outcome is achieved.

### Data management

The study is managed by the Chief Investigator with support from DCTU.

Study data are recorded in each patient’s medical notes before being entered onto electronic Case Report Forms (e-CRFs). Data entered into the e-CRF must be consistent with the information in the medical notes. Discrepancies are noted and explained. Un-anonymised data are held on site in accordance with local Trust policies. Patients are identified by a unique study number at enrolment. All data passed to DCTU have patient identifiers removed, except date of birth, gender, ethnicity and unique study ID. All data are handled in a confidential manner by DCTU, the research team and by members of the Data Monitoring Committee (DMC) and Trial Steering Committee (TSC).

### Statistical methods

The null hypothesis is that there will be no difference in the proportion of patients receiving RBC transfusion after manubrium-limited ministernotomy when compared to conventional sternotomy for AVR.

This trial will determine if manubrium-limited ministernotomy is an appropriate clinical alternative to the existing operation (conventional sternotomy) in terms of RBC transfusion requirements in the 7 days following index surgery. An analysis of the primary endpoint will be conducted using Fisher’s exact test. A sensitivity analysis will also be performed for the primary endpoint using a logistic regression model to account for potential confounders and stratification factors. Continuous outcomes will be analysed using general linear models. Correlation between repeated measures per patient will be appropriately accounted for in the linear models where applicable. Binary data will be analysed using logistic regression where there are no repeated data per patient. Repeated binary data will be analysed using generalised estimating equations. Stratification factors and chance baseline imbalances following randomisation will be explored for the primary and secondary outcomes.

Analysis will follow intention-to-treat principles with patients analysed according to the surgery allocated by randomisation and irrespective of surgery received, subsequent management or events [26]. Every effort will be made to retain and include all patients who receive surgery as part of the trial.

A prospective economic evaluation is integrated into the trial design and applies an NHS perspective to the inclusion of costs. Mechanisms of missingness within the data will be explored, and multiple imputation methods will be applied to impute missing data and minimise bias. Imputation sets will be used in bivariate analysis of costs and QALYS to generate incremental cost per QALY estimates and credible intervals [27–29]. It is anticipated that incremental costs and benefits will be captured within the trial, although extrapolated economic modelling will be considered if appropriate. Findings will be presented on the incremental cost-effectiveness ratio (ICER) plane and using cost-effectiveness acceptability curves (CEACs).

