### Trial design

This is a single-centre, single-blind, randomised controlled superiority trial comparing patients undergoing AVR via manubrium-limited ministernotomy (intervention under study) or conventional median sternotomy (control arm/usual care); randomisation will be performed using random permuted blocks with a 1:1 allocation.

The manubrium-limited ministernotomy versus conventional sternotomy for aortic valve replacement (MAVRIC) trial protocol was written in accordance with the Standard Protocol Items: Recommendations for Interventional Trials (SPIRIT) checklist (see Additional file 1) [19, 20]. The schedule of this trial is shown in Fig. 1.

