### Sample size calculation

This trial will determine if manubrium-limited ministernotomy is an appropriate clinical alternative to the existing operation (conventional sternotomy) in terms of RBC transfusion requirements in the 7 days following index surgery. Currently, there is clinical and policy equipoise with no intention to extend the use of the new procedure until high-quality randomised controlled trial evidence is available.

Using Fisher’s exact test, 90% power, 5% alpha, 260 patients are required to detect a 17% reduction in the proportion of patients requiring RBC transfusion (13% compared with 30%), using a two-sided test. Recruitment will continue until the target sample size is reached and 260 patients are contributing to the primary outcome.

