### Allocation

Following consent, eligible patients are randomised to receive AVR by manubrium-limited ministernotomy or by conventional sternotomy following confirmation of eligibility. Randomisation is made using a permuted block randomisation, stratified by logistic EuroSCORE [24] (low risk 0–3.50%, moderate risk 3.51–7.5% and high risk >7.5%) and by pre-operative Hb (90–125 g/L, 126–140 g/L, >140 g/L). A web-based randomisation system, managed by Durham Clinical Trials Unit (DCTU), will ensure concealment of allocation.

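### The primary Fisher's exact test leaves out the two factors used to stratify randomisation: valid and adequately powered, but conservative, with about 1.5 to 3.4 points of power unused at the same N

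*Protocol article*

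**What the plan says.** Under Allocation, the Protocol article states: "Randomisation is made using a permuted block randomisation, stratified by logistic EuroSCORE" in three bands, and "by pre-operative Hb (90–125 g/L, 126–140 g/L, >140 g/L" in three more. That gives 3 × 3 = 9 strata, with 1:1 allocation in permuted blocks (Trial design).

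Under Statistical methods, the primary test is fixed: "An analysis of the primary endpoint will be conducted using Fisher’s exact test". No stratified or adjusted version of it is named. The strata appear in the next sentence, in a secondary role: "A sensitivity analysis will also be performed for the primary endpoint using a logistic regression model to account for potential confounders and stratification factors". The same section adds that stratification factors and chance baseline imbalances will be explored.

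The sample size rests on the same test: "Using Fisher’s exact test, 90% power, 5% alpha, 260 patients are required to detect a 17% reduction" ("13% compared with 30%), using a two-sided test"). Planned test and planned N therefore agree.

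**The concern.** Blocking within strata forces the arms to be alike on EuroSCORE and haemoglobin. If those factors predict transfusion, the difference between arms varies less than an unstratified test assumes. The precision bought by the design then shows up as a test that rejects too rarely. Haemoglobin is a plausible predictor, because a post-operative value below 80 g/L is one of the three red-cell transfusion criteria (Blood and blood product usage following surgery). Fisher's test is already conservative because it is discrete, so the two effects add.

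At stake is efficiency, not validity. Conservatism matters most if the true effect is smaller than planned or the p-value is borderline. In that case the primary Fisher result and the adjusted sensitivity result could disagree, and choosing between them after seeing the data would not be credible.

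**Working it through.** **Inputs from the Protocol article.** Rates 30% and 13%; two-sided alpha 0.05; power 90%; Fisher's exact test; 260 patients contributing, so 130 per arm; nine strata.

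**Inputs assumed, because the article does not give them.** Nine equally likely strata; block size 4 in the first simulation below; an odds ratio (OR) per step of haemoglobin category and per step of EuroSCORE category, varied over a range.

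**1. The plan's own figure.** Exact power is the sum, over all pairs of event counts (x, y) with Fisher p ≤ 0.05, of Bin(x; n, 0.13) × Bin(y; n, 0.30).
- n = 129 per arm: 89.96%.
- n = 130 per arm: 90.23%.

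N = 260 reproduces exactly.

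**2. True size at 130 per arm, no strata effect.** The same sum with a common rate in both arms; 21.5% is the mean, (30 + 13)/2.

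| Common rate | Fisher | Uncorrected chi-square |
|---|---|---|
| 13% | 3.26% | 4.89% |
| 21.5% | 3.57% | 4.99% |
| 30% | 3.65% | 5.04% |

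Uncorrected chi-square power is 92.47%, against 90.23% for Fisher; 119 per arm would give it 90%. This gap comes from discreteness alone.

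**3. Adding the strata.** In stratum k let n be the patients, t and c the numbers in the two arms, m the events, and x the events in the intervention arm. The CMH statistic without continuity correction is [Σ(x − tm/n)]² / Σ[t c m (n − m) / (n²(n − 1))], compared with 3.84. Logistic is a likelihood-ratio test of treatment with main effects for both factors. There were 4,000 simulated trials per row, with overall rates of 30% v 13% for power and a common 21.5% for size.

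| OR per step, Hb / EuroSCORE | Power: Fisher / CMH / logistic | Size: Fisher / CMH / logistic |
|---|---|---|
| 1 / 1 | 91.0 / 92.5 / 93.2% | 4.2 / 5.2 / 5.5% |
| 1.5 / 1.25 | 91.0 / 93.0 / 93.4% | 3.8 / 5.2 / 5.6% |
| 2 / 1.5 | 91.8 / 93.7 / 93.9% | 3.2 / 4.6 / 4.9% |
| 3 / 2 | 92.7 / 95.9 / 96.0% | 2.9 / 4.9 / 5.4% |

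Monte Carlo standard error is about 0.3 to 0.5 points. The 4.2% in the first row exceeds the 3.57% of step 2 because simulated arms are rarely exactly 130 and 130, and Fisher's test is less discrete when arms differ slightly. A further simulation, reaching an odds ratio of 4 per haemoglobin category, put Fisher's size at 2.4% at the strong end with CMH still near 5%.

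**4. Splitting the gain.** A separate simulation of 4,000 trials per row compared Fisher, the unadjusted uncorrected chi-square and CMH. Chi-square minus Fisher is the discreteness part; CMH minus chi-square is the stratification part.

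| OR per step, Hb / EuroSCORE | Fisher | Chi-square | CMH | Discreteness | Strata | CMH with continuity correction |
|---|---|---|---|---|---|---|
| 1.5 / 1.25 | 91.6 | 93.1 | 93.3 | 1.5 | 0.2 | 91.1 |
| 2 / 1.3 | 91.4 | 93.2 | 94.0 | 1.8 | 0.8 | 91.4 |
| 3 / 1.4 | 92.1 | 93.6 | 95.3 | 1.5 | 1.7 | 92.7 |
| 4 / 1.5 | 92.6 | 94.2 | 96.3 | 1.6 | 2.1 | 94.5 |

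The total gain runs from 1.5 points with uninformative strata (92.5 − 91.0) to about 3.4 with strong ones; single runs at the strong end gave 3.2 to 3.7, a spread that simulation error can explain. A continuity correction removes all or most of the gain (−0.5, 0.0, 0.6 and 1.9 points over Fisher) and takes the size down to about 3%.

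**5. Can the data carry the model?** Expected events are 130 × 0.30 + 130 × 0.13 = 39 + 17 = 56, for five parameters (one treatment, two haemoglobin, two EuroSCORE), or about 11 each.

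**The case against.** The strongest reply is that the plan is coherent and meets its own target. It was sized on the test it uses, that test has 90.2% power, and its error rate lies below 5%. This stands. A reader might infer that the trial is underpowered or the sample size wrong; the reproduction in step 1 rules both out.

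A second reply is that stratification is not the main cause. This also stands in large part: about 1.5 points of the gain come from discreteness, whatever the strata do. The stratum part of 0 to 2 points depends on prognostic strength that the article does not quantify. The haemoglobin criterion makes a link plausible without giving its size, and the other two criteria concern bleeding.

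Third, the adjusted model is already planned. That is true, but only as a sensitivity analysis and together with unnamed further confounders.

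Two stronger readings are not supported. One is that the primary result would carry no effect estimate. Naming a test does not exclude reporting a risk difference with an interval, and a condensed article commonly leaves this to the SAP. The other is that unspecified confounders contaminate the primary model; they belong to the sensitivity model.

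Finally, recruitment began in March 2014 and clinicians are not blinded, so changing the primary test is a real amendment that needs justification. That adds to the cost but does not remove the reason for the change.

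**Conclusion.** The point holds as a modest loss of efficiency. The primary test ignores the factors by which patients are randomised, and it is conservative: size 3.3 to 3.7% at 130 per arm from discreteness alone, and roughly 2.4 to 3.6% if the strata predict transfusion. An uncorrected stratified test would keep its size near 5% and add about 1.5 to 3.4 points of power at N = 260.

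The exact size and power of Fisher's test need only the article's own figures. The gain attributed to the strata rests on assumed equal strata and odds ratios of 1 to 4 per haemoglobin category, and could be close to zero. The planned 90% power is met as written.

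**What to change.** By amendment, before any unblinded data are analysed, make the primary analysis one that accounts for the two randomisation factors only. Either form would serve:
- a CMH test over the strata, stated to be without continuity correction; or
- logistic regression with main effects for EuroSCORE and haemoglobin. A full 3 × 3 interaction is best avoided, as some of the nine cells may be sparse.

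Report a stratified or marginal risk difference with 95% CI, the scale on which the trial is sized. Keep Fisher's test, and separately the model with further confounders, as sensitivity analyses.

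The cost is a protocol amendment with a short justification, and matching SAP text. N stays at 260, and no new data are needed because both factors are recorded before randomisation. The logistic likelihood-ratio form may run slightly above 5% (up to about 5.6% in step 3); if strict size control matters most, the CMH form is the safer choice.

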#### Secondary outcomes

Secondary outcomes are:The proportion of patients who receive a RBC transfusion during the intra-operative period and the entire post-operative hospital stayThe mean number of RBC units transfused during the intra-operative period, post-operative period (within the 7 days following AVR surgery) and the entire post-operative hospital stayThe proportion of patients receiving blood product transfusions during the intra-operative period, within the 7 days following AVR surgery and during the entire hospital stayThe mean number of blood product transfusions received during the intra-operative period, within the 7 days following AVR surgery and during the entire hospital stayMean post-operative blood loss (millilitres) measured from chest drains at 6 and 12 hours, and at the time of drain removal, following AVR surgeryOperative success as defined by transthoracic echocardiographic assessment of left ventricular function, and degree of aortic regurgitation, within 6 weeks of AVR surgeryMean post-operative changes in haemoglobin (Hb) within the index hospital stayMean post-operative changes in inflammatory markers on admission to CICU and on day 1 following AVR surgeryProportion of patients reporting moderate or severe post-operative sternal wound pain, measured daily using an 11-point numerical rating scale developed by the trial team, until patient is fit for hospital discharge, and at 6 and 12 weeks following AVR surgeryRates of re-operation following index AVR surgery until 12 weeksRate of conversion to conventional AVR during index surgeryChanges in forced expiratory volume and forced vital capacity on days 3 and 4 and at 6 weeks following AVR surgeryEuroQoL EQ-5D-3L [21] scores, captured at baseline and on day 2, and 6 weeks and 12 weeks following AVR surgery, will be converted to health status scores using the value set (time trade-off) [22] and provide patient-level quality-adjusted life year (QALY) estimates as a health outcome [23]. The EQ-5D-3L is a validated, self-reported outcome measure consisting of five dimensions: mobility, self-care, usual activity, pain/discomfort, anxiety/depression. Each dimension has three levels of response.Mean time at which patients are fit for discharge from hospital following AVR surgeryHealth care utilisation during hospital stay and following discharge to 12 weeks, from medical note review, GP records and patient reportsCost and cost effectiveness estimated from QALY estimates and health care utilisation valued using national reference costs to 12 weeksRates of related adverse events during the 12 weeks following surgery including severity.

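### The planned credible interval for cost per QALY is not a valid uncertainty interval if the QALY-difference draws span zero; intervals for incremental cost, QALYs and net benefit should replace it (minor)

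*Protocol article*

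**What the plan says.** The economic paragraph of the Statistical methods section plans multiple imputation followed by a joint analysis of costs and QALYs: "Imputation sets will be used in bivariate analysis of costs and QALYS to generate incremental cost per QALY estimates and credible intervals". The noun before the intervals is the cost per QALY, so the natural reading is an interval on the ratio. The paragraph then adds: "Findings will be presented on the incremental cost-effectiveness ratio (ICER) plane and using cost-effectiveness acceptability curves (CEACs". It expects the relevant costs and benefits to arise within the trial, "although extrapolated economic modelling will be considered if appropriate".

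Under Secondary outcomes, QALYs come from EQ-5D-3L scores "captured at baseline and on day 2, and 6 weeks and 12 weeks following AVR surgery", and cost-effectiveness is assessed to 12 weeks. The article gives no expected utility or cost difference, no SD for either and no willingness-to-pay threshold. It does not say how the interval would be formed if the draws fall in more than one quadrant of the plane.

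**The concern.** A percentile interval has meaning only if its values can be ordered from less to more favourable. A cost-per-QALY ratio has that order while the QALY difference keeps one sign. Once the draws fall on both sides of zero, the order is lost:

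- A negative ratio can mean cheaper and better, or dearer and worse.
- A positive ratio can mean dearer and better, or cheaper and worse.
- Draws with a QALY difference near zero run to very large values of either sign.

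Cost-effectiveness is a named secondary outcome, and the Trial rationale section cites NHS resources as a reason for the trial. An interval printed beside the ICER would be quoted as its error bar. If the draws straddle zero, it would not be one.

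**Working it through.** **1. The plan's own figure.** The only sample size stated is for transfusion: "90% power, 5% alpha, 260 patients are required to detect a 17% reduction" ("13% compared with 30%), using a two-sided test"), with 1:1 allocation. For 30% against 13%, two-sided, the normal approximation gives 121 per arm (242 in total) without a continuity correction and 133 per arm (266) with it. Exact enumeration of Fisher's test at 130 per arm gives 90.2% power, so 260 reproduces. That number was not chosen for QALYs, and the plan has no economic figure to reproduce.

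**2. Inputs for the economic check.**
- From the article: 130 per arm and a 12-week horizon (12/52 = 0.231 year).
- Assumed: mean utility difference Δu of 0 to 0.10; between-patient SD of mean utility of 0.15 to 0.30; cost SD of GBP 4,000; uncorrelated normal draws; threshold of GBP 20,000 per QALY.

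**3. When the QALY difference spans zero.** The difference is Δu × 12/52 and its standard error is SD × 12/52 × √(2/130). The factor 12/52 cancels in their ratio:

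z = Δu / (SD × √(2/130)), with √(2/130) = 0.124.

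The 95% interval excludes zero once Δu exceeds 1.96 × 0.124 × SD. The last three columns give the share of draws with a negative QALY difference.

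| SD | Δu needed | Δu = 0.02 | Δu = 0.05 | Δu = 0.10 |
|---|---|---|---|---|
| 0.15 | 0.036 | 14% | 0.4% | 0.0% |
| 0.20 | 0.049 | 21% | 2.2% | 0.0% |
| 0.25 | 0.061 | 26% | 5.3% | 0.1% |
| 0.30 | 0.073 | 30% | 9.0% | 0.4% |

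At Δu = 0 the share is 50% for every SD.

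**4. A case that breaks down.** Take SD 0.25, Δu = 0.02 and a cost difference of +500.
- QALY difference: 0.02 × 12/52 = 0.0046, with SE 0.0072.
- Cost SE: 4,000 × 0.124 = 496.
- 95% percentile limits of the ratio over 400,000 draws: about GBP −0.99 million to +1.09 million per QALY.
- Draws by quadrant: 62.5% dearer and better, 21.8% dearer and worse, 11.6% cheaper and better, 4.0% cheaper and worse.
- Of the negative ratios, 21.8/(21.8 + 11.6) = 65% are draws where the ministernotomy is dominated. The rest are draws where it dominates.
- The acceptability curve at 20,000 is still well defined, at 0.21.

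**5. A case that does not.** Take SD 0.25, Δu = 0.10 and a cost difference of +1,500. The limits are about GBP 21,000 to 184,000, with 99.8% of draws in one quadrant. That interval can be read in the ordinary way.

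**6. A second set of assumptions.** Take a baseline-adjusted SD of 0.18, so the SE is 12/52 × 0.18 × 0.124 = 0.0052, and a cost SE of 300.
- *Gain 0.006 QALY, cost −100:* 12% of draws have negative QALYs and the ratio interval is about GBP −420,000 to +371,000. Net benefit at 20,000 is 20,000 × 0.006 + 100 = 220. Its SE is √((20,000 × 0.00515)² + 300²) = 317, so its interval is about −400 to +840. About 8% of the negative ratios are dominated draws.
- *Gain 0.006, cost +300:* P(QALY < 0) = 0.122 and P(cost > 0) = 0.841. The dominated share of negative ratios is (0.122 × 0.841)/(0.122 × 0.841 + 0.878 × 0.159) = 42%.
- *Gain 0.0115, cost −100:* only about 1.3% of draws have negative QALYs. The interval is about −115,000 to +72,000. Restricting to positive-QALY draws barely changes it (−109,000 to +63,000). Its width comes from a cost SE three times the cost difference, not from mixed conclusions.

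**The case against.** Four points can be made for the plan.

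**The problem is conditional.** A reader might infer that over 12 weeks the QALY difference must lie near zero, so that the interval is bound to fail. The article does not support this. It states no utility effect, and step 5 shows a case where the interval is sound. Nor is the short horizon the cause: it shrinks the difference and its standard error by the same factor. This part of the objection stands.

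**The plan already shows the joint uncertainty properly.** A reader might infer that the economic conclusion as a whole would be invalid. It would not. The analysis is bivariate, and the plane and acceptability curves remain valid when the QALY difference crosses zero. The curve is the probability of positive net benefit at each threshold. This also stands, but a valid graph does not make the printed interval valid.

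**The wording is condensed.** It does not specify percentile limits of the ratio, it could also cover intervals on costs and QALYs separately, and it cites methods references not available here. A fuller analysis plan may settle the matter. That limits the weight of the point. Still, the output named is an interval for cost per QALY, and nothing shown restricts it.

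**It is a reporting detail of a secondary outcome.** That is correct, and it sets the severity.

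**Conclusion.** The point holds in conditional form and is minor. If the draws for the QALY difference have real mass on both sides of zero, the planned interval on the ratio mixes opposite conclusions and should not be reported as uncertainty. With 130 per arm and an assumed SD of 0.15 to 0.30, that covers mean utility differences smaller than about 0.036 to 0.073, or 0.008 to 0.017 QALY after multiplying by 12/52.

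Effects of that size are a realistic case to plan for. Both arms receive a valve replacement through different incisions, several of the hoped-for benefits concern recovery and may fade during follow-up, and the sample size was set for transfusion. The utility, cost and threshold values are all assumptions, as are the zero correlation and normality. The logical defect of the ratio interval does not depend on them; how likely it is to matter does. The primary outcome, the sample size and data collection are unaffected.

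**What to change.** Replace the interval on the ratio with wording such as:

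> *Credible intervals will be reported for incremental cost, incremental QALYs and incremental net monetary benefit at pre-stated willingness-to-pay thresholds. The ICER will be given as a point estimate, with an interval only if essentially all draws lie in one quadrant of the cost-effectiveness plane.*

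Keep the plane and the acceptability curves as planned. The strict requirement for an orderable ratio is that the QALY difference keeps one sign. The one-quadrant rule is somewhat stricter, but it is simple to state and check.

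The thresholds should be fixed before the data are analysed. The change costs one sentence in the analysis plan. Every quantity comes from the same bivariate draws, so no new data or modelling is needed.
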